**Fig 1 pone.0314459.g001:**
[figure not shown]
Study design.

### 2.4. Measures

At Survey 0, participants will be asked to provide basic demographic characteristics (i.e., age, number of children, level of educational attainment). The primary outcome of interest, parents’ CSA-related awareness and parent behaviors will be assessed using the Assessment of SmartParents’ Knowledge (ASK) [18]. The 15-item ASK, rated on a 5-point Likert scale (i.e., Strongly Disagree to Strongly Agree), provides an indicator of parents’ CSA-related awareness (e.g., “Most sexual abuse victims are abused by someone they know”) and intention to use protective behaviors (e.g., “I have talked to my child about how to protect themselves from being sexually abused”).

To explore CSA-related preventive behaviors used by the parent, at Survey 0 all parents will be asked to complete the 10-item preventive behaviors questionnaire (PBQ) [30]. On the PBQ, parents to report how frequently in the past month (i.e., never [0], sometimes [1–5 times a month], or a lot [6–10 times a month]) they performed a named preventive behavior (e.g., “Educated [their] child about the difference between safe and unsafe touches” or “Modeled or talked about privacy in the home.”). The PBQ, thus, measures actual use of protective behaviors.

To examine general parenting modalities, all parents will be asked to complete the 16-item Knowledge of Parenting Strategies Scale (KOPSS) [31] at Surveys 0 and 1. The KOPSS asks parents a set of multiple-choice questions about parenting practices (e.g., “It is 5 minutes before dinner time and a child is throwing a tantrum for a cookie. What should mum do?”) and awards a parent one point per correct answer. Higher scores indicate a greater degree of use of desired parenting qualities.

There is a paucity of standardized measures to demonstrate actual use of protective behaviors. We will leverage this study to pilot a questionnaire format for the Parents Use of Behavioral Strategies Interview (PUBSI), a project generated assessment tool, at Survey 2. The 23-item assessment will evaluate parent use of protective behaviors using mixed response types including: yes or no questions; a 5-point Likert scale assessing confidence; and short answer textboxes. Examples of questions include “Have you made changes to your home environment to protect your child from sexual abuse?”, “How confident are you that your child knows who to go to (or talk to) if they feel unsafe?”, and “What names does your family use to refer to private parts?”. Change in the prevalence of CSA is the ultimate outcome of interest; however, the stigma of and mean time to disclosure [32–34] reduce the feasibility of using administrative data for outcomes in any CSA intervention research. In addition, verifying self-report accuracy is beyond the scope of this study. The outcome of interest in the current study is the increased use of CSA-related knowledge and self-reported use of protective behaviors.

Participants in the experimental group will also be asked to complete a satisfaction form on Survey 1 (delivered 1-month post-workshop, Fig 1). This form asks the parents about their perceptions on preventing CSA before and after the workshop as well as the acceptability of the program and how likely they are to recommend the *Smarter Parents* workshop to other parents. To understand the ways in which parents interacted with the workshop, parents will be asked to report the device used to join the workshop (i.e., desktop computer, laptop, tablet, etc.). Parents will also be asked to provide suggestions on how to make the workshop more accessible to caregivers and how to promote the workshop in their community (e.g., fliers in school, school-based apps, counselor recommendations, etc.).

### 2.5. Incentive structure

Participants in both groups will be eligible to receive up to $100 in Amazon e-gift cards distributed via participant-provided email. Participants in the control group will receive a $20 Amazon e-gift card after completion of Survey 0. Those in the experimental group will receive this $20 Amazon e-gift card after completion of Survey 0 and verified attendance in a *Smarter Parents* workshop provided by sites. After the completion of Survey 1, all participants will receive a $30 Amazon e-gift card and a $50 Amazon e-gift card after completion of Survey 2. This incremental incentive structure is a common approach implemented by our team to promote participant retention throughout the course of the study.

### 2.6. Statistical plan

#### 2.6.1. Sample size and power

Without a strong literature base to refer to for universal parent-focused CSA prevention programs, we used prior research of the selective parent-focused program [19] and a meta-analysis of parent-focused child maltreatment prevention interventions [35] to inform our effect size estimation. For the current quasi experimental study, we assumed a conservative pre-post correlation of .7, specified a small effect size of a Cohen’s *d* of .2, and set the measure of significance, α, to .10 (i.e., adopted decision-priority perspective) [36]. Using a power calculator [37], the results of our power calculation indicated a need for 317 total participants (158 per condition). However, accounting for an estimated 30% attrition (i.e., loss to follow-up), we will aim to recruit a total of *N* = 412 participants, *n =* 206 per condition.

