#### 2.6.2. Analytic plan

Quantitative analyses of the resulting pre- and post-workshop data will examine whether levels of CSA-related awareness and intention to use protective behaviors are greater for parents who participated in a Smarter Parents workshop in comparison to those who did not. As we will have longitudinal quasi-experimental data, we will use a difference-in-difference (DID) approach to analysis [38]. DID is appropriate when (a) randomization at the individual level is not possible and (b) the goal is to examine the effect of a specific intervention by comparing changes overtime among those who received the intervention (experimental) and those who did not (control). Using the DID regression framework, meditation analyses will examine potential differential effects by parent characteristics (e.g., demographics, initial parenting strategies [KOPSS] and actual use of protective and preventive behaviors [PBQ]).

To understand the impact of recruitment materials on parental engagement, we will first qualitatively code the strategies used on recruitment materials provided by the sites (e.g., theoretical framing, image, testimonial, incentive, etc.). We will quantify which strategies were used most consistently across the experimental site. We will also map types of ads used by the sites to registration/attendance numbers reported on the implementation forms. Participant responses on the satisfaction form (e.g., “Do you have any suggestions on how to promote Smarter Parents in your community?”) will be coded thematically to inform sites recruitment efforts in the future. All data will be made available in the lead authors’ university data repository once the study is complete.

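### The evaluable total of 317 matches a baseline-adjusted (ANCOVA) calculation at 80% power; the difference-in-differences analysis that the plan names would, with a single follow-up, have about 74% power at 317 and need about 373

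*Protocol article*

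**What the plan says.** Section 2.6.1 of the protocol article gives the inputs: "we assumed a conservative pre-post correlation of .7, specified a small effect size". The effect is a standardised mean difference (d) of 0.2, and alpha is 0.10. The section reports that a power calculator "indicated a need for 317 total participants (158 per condition"). It then allows for 30% attrition and sets the recruitment target at 412, 206 per condition. It does not state the target power, whether the test is one- or two-sided, the model behind the calculation, or the SD by which d is scaled.

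Section 2.6.2 names the analysis: "we will use a difference-in-difference (DID) approach to analysis". It explains DID as a comparison of changes over time between the two groups and justifies it by the absence of randomisation. The article mentions no baseline-adjusted model. Section 2.3 schedules a baseline survey and two follow-up surveys, at 1 and 3 months. The article does not say which follow-up, or what combination, forms the DID contrast.

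**The concern.** A pre-post correlation reduces the required sample size by an amount that depends on the estimator. Regression adjustment for baseline leaves a fraction 1−r² of the outcome variance. A difference of change scores leaves 2(1−r), which is larger for every r below 1. The ratio of the two is 2/(1+r), or 1.18 at r = .7. If the sample size was computed with the first factor and the data are analysed with the second, the study has less power than the team believes it planned for.

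In this study the two estimators are not interchangeable. Groups are formed by workshop attendance, so they may differ at baseline, and the two approaches then rest on different assumptions. The plan chose DID for that reason and cannot also take credit for the efficiency of baseline adjustment. At stake is how a null or borderline result would be read, with an alpha already relaxed to .10.

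A second, smaller matter is the description of .7 as conservative. Power falls as r falls, so .7 is conservative only if the true correlation is expected to be higher. The article gives no basis for that; the sources it cites in Section 2.6.1 are said to inform the effect size.

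**Working it through.** **Inputs.** From Section 2.6.1: d = 0.2, r = .7, alpha = .10, stated total 317 (158 per condition). From Section 2.6.2: DID as the analysis. Assumed, because the article does not print them: two-sided test, 80% power, equal allocation (as for the 206 per condition), d in raw-score SD units, one baseline and one follow-up.

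**Formula.** Per arm, n = 2·vf·(z₁₋α/₂ + z₁₋β)² / d², where vf is the variance factor. Here z₀.₉₅ + z₀.₈₀ = 1.645 + 0.842 = 2.486, and its square is 6.183.

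**Step 1: the plan's own figure.** With vf = 1 − 0.7² = 0.51:
- n = 2 × 0.51 × 6.183 / 0.04 = 157.7, so 158 per arm.
- With the t correction, N = 316 gives power .7993 and N = 317 gives .8004. So 317 is the smallest total that reaches 80%.

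Both stated numbers are reproduced. A one-sided test at alpha .05 gives the same result; Section 2.6.1 states .10.

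**Step 2: the named analysis at the same inputs.** With vf = 2(1 − 0.7) = 0.60:
- n = 2 × 0.60 × 6.183 / 0.04 = 185.5, so 186 per arm and 372 in total; 373 with the t correction.
- Power at N = 317 is .742.
- Minimum detectable d at N = 317 and 80% power is about 2.486 × √(4 × 0.60 / 317) = 0.216 (0.217 with the t correction). The ANCOVA figure is 0.200.

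**Step 3: could 317 have come from a DID calculation?** At alpha .10 and one follow-up, the nearest DID totals are 325 (75% power, two-sided) and 324 (85% power, one-sided). Neither gives 317 and 158. A post-only comparison at 80% power needs 620.

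**Step 4: how far the result depends on the assumptions.**

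| Reading of the DID contrast (two-sided .10, 80% power) | Total needed |
|---|---|
| One follow-up, d in raw-score SD | 373 |
| Mean of both follow-ups, all correlations .7; vf = (1 + 0.7)/2 + 1 − 2(0.7) = 0.45 | 280 |
| One follow-up, d in change-score SD | 620 |

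**Step 5: at the number left after attrition.** 412 × 0.70 = 288.4, about 288. Power there is about 77% with the ANCOVA factor and about 71% with the single-follow-up DID factor. The minimum detectable d for DID is about 2.486 × √(4 × 0.60 / 288) = 0.227. Part of this loss is a separate matter: 412 is 317 × 1.3, whereas 317 / 0.70 = 453. At 288, the estimator alone accounts for about 6 points (77% to 71%).

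**Step 6: sensitivity to r (illustrative values, not from the article).** Single-follow-up DID power at 288 is about 60% at r = .6 and 52% at r = .5.

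**The case against.** The strongest objection is that no printed figure is contradicted. A reader might infer that the article claims 80% power and fails to deliver it. It does not print 80%, and two-sided ANCOVA at 80% is a reconstruction from one match. That stands as a limit on the wording, although an exact match on both 317 and 158 at the stated alpha and customary power is strong evidence.

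Second, 373 is one scenario. The study has two follow-ups and Section 2.6.2 speaks of a DID regression framework. A contrast that averages both follow-ups, with correlation .7 throughout, would need about 280, and 317 would then give about 84% power. This also stands: a reader should not take 373 as the established requirement. But the article describes no such averaging and supplies a single pre-post correlation, so the averaged reading cannot be credited to the plan as written.

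Third, the estimator mismatch alone is modest: d of 0.217 against 0.200. The 71% and d of 0.23 also contain the attrition arithmetic and should not be charged wholly to this point. That is right.

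Fourth, a reader might infer that .7 is too high or that the word conservative is wrong. The article does not support that. If the team's sources show higher correlations, .7 is conservative in the correct sense. What remains is that the basis is not given.

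Fifth, target power and sidedness may sit in a fuller document. Their absence alone would be no finding. The finding is that the article prints both a number and an analysis, and the number fits a different analysis.

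**Conclusion.** The sample size in Section 2.6.1 is consistent with a baseline-adjusted comparison and not with the DID analysis in Section 2.6.2 under its plainest reading. For a single-follow-up DID with d in raw-score SD units, an implied power of 80% becomes about 74% at 317 evaluable, and about 373 would be needed to restore it. The 80% and the two-sided test are inferred. The factor of 1.18 between the two requirements depends only on r = .7 and the single-follow-up contrast, not on the power chosen.

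The mismatch does not bias the DID estimate or invalidate the analysis. It affects the precision the study can claim and how a null result should be read.

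**What to change.** Rewrite the sample-size paragraph in Section 2.6.1:

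- Recompute with the variance of the DID contrast actually planned, stating which follow-up or follow-ups it uses.
- State the target power, the sidedness and the SD that scales d.
- Restate the power or minimum detectable effect. For a single-follow-up DID this is about 74% for d = .2 at 317 evaluable. At the 288 left if 30% of 412 are lost, it is about 71%, or d of about 0.23 at 80% power; part of that shortfall belongs to the attrition arithmetic.
- Give the basis for calling r = .7 conservative. If results at lower r are shown, label them as illustrative.

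The cost is one rewritten paragraph and, under the single-follow-up reading, a less favourable stated power. No change to enrolment or to the analysis is required.

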**Methods:**

This study will use a quasi-experimental design (target *N* = 412) to examine potential gains in CSA-related awareness and intentions to use protective behaviors among parents who participate in a universal parent-focused CSA prevention workshop, *Smarter Parents*. *Safer Kids*., compared to those who do not. Participants in both the control (*n* = 206) and experimental group (*n* = 206) will complete 3 survey assessments: Survey 0 (baseline), Survey 1 (1-month), and Survey 2 (3-month follow-up). The experimental group will participate in a *Smarter Parents*. *Safer Kids*. workshop between the Surveys 0 and 1. We will use data collected from the baseline to measure potential mediators of CSA-related awareness and intention to use protective and preventive behaviors. In adjacent efforts to enhance the curriculum’s reach with future dissemination and implementation, we will also explore the impact of recruitment materials and strategies on parental engagement.

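### The 30% attrition allowance was applied as 317 × 1.3 = 412 instead of 317/0.7 = 453, so the recruitment target falls about 29 short of the stated need if attrition is as expected

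*Protocol article*

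**What the plan says.** Section 2.6.1 (Sample size and power) builds the sample size in two steps.

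- **Base requirement.** The inputs are a correlation ("we assumed a conservative pre-post correlation of .7"), an effect size ("specified a small effect size of a Cohen’s *d* of .2") and a significance level ("set the measure of significance, α, to .10"). The calculation "indicated a need for 317 total participants (158 per condition").
- **Attrition step.** The text continues: "accounting for an estimated 30% attrition (i.e., loss to follow-up), we will aim to recruit a total of" 412, or 206 per condition.

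The section gives no power figure, does not say whether the test is one- or two-sided, and does not name the model behind the calculation. The target of 412, the 206 per group, or both, reappear in the abstract's Methods, in section 1.3 and in section 2.3. No section gives another attrition rate, a replacement rule or a re-estimation rule.

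**The concern.** The article defines the 30% as loss to follow-up, so it is a fraction of the people enrolled. To be left with a required number, that number must be divided by the fraction expected to stay (0.7). The target of 412 is what results from adding 30% to the required number, which is a smaller allowance.

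The three stated figures (317 needed, 30% lost, 412 recruited) therefore cannot all hold. The 30% is the investigators' own expectation, so the shortfall is the planned case and not a worst case. A reader who later interprets a null result would believe the design had allowed for 30% attrition when it had not.

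**Working it through.** **Inputs, all from section 2.6.1:** required N = 317 (158 per condition); attrition 30%; target 412 (206 per condition); d = 0.2; r = 0.7; α = .10.

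**1. Reproduce the stated target.**
- 317 × (1 + 0.30) = 412.1, the stated 412.
- Per condition: 158 × 1.3 = 205.4, rounded up to the stated 206.

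**2. Apply the allowance as a share of those recruited.**
- N = 317/(1 − 0.30) = 452.9, so 453, or 454 with equal groups (227 each).
- Starting from 158 per condition: 158/0.7 = 225.7, so 226 per condition (452 in total). The one-participant gap between 317 and 2 × 158 = 316 makes no difference here.

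**3. What 412 delivers.**
- 412 × 0.7 = 288.4, about 288; 206 × 0.7 = 144.2, about 144 per condition.
- Shortfall: 317 − 288 = 29, or 29/317 = 9% of the requirement.
- Largest attrition that still leaves 317: 1 − 317/412 = 23.1%.
- Put another way, 412 − 317 = 95. That is 30% of the 317 who must remain, but only 23% of the 412 who enrol.

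Steps 1 to 3 use only the three stated figures and do not depend on how 317 was obtained.

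**4. Effect on power (assumptions needed).** Power, sidedness and model are not stated, so the candidates were tested against 317. Take the SD of the outcome as 1. The residual variance is 1 − r² = 0.51 for a baseline-adjusted comparison and 2(1 − r) = 0.60 for a change score.

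- Formula: n per condition = 2 × variance × (z_α + z_power)² / d².
- Baseline-adjusted, two-sided .10, 80% power: 2 × 0.51 × (1.645 + 0.842)² / 0.04 = 157.7, so 158 per condition. This matches the protocol's 158.
- Change score, one-sided .10, 85% power: 324 in total, within 3% of 317.
- Change score at 80% power: 372 two-sided and 272 one-sided. Neither matches.

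| Assumed model and test | Power at 158 per condition | Power at 144 per condition |
|---|---|---|
| Baseline-adjusted, two-sided | 80.1% | 76.8% |
| Change score, one-sided | 84.5% | 81.8% |
| Change score, two-sided | 74.2% | 70.7% |

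For the first row an F-test calculation gives 80.0% at N = 317 and 76.6% at N = 288. The loss is roughly 3 points in every row.

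**The case against.** The inflation arithmetic itself has no good answer: the figures are legible and repeated, and nothing elsewhere makes 412 sufficient. It might be said that partial responders could still contribute to a longitudinal model. That does not help, because the protocol itself names 317 as the need and presents 412 as covering 30% loss to follow-up.

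The objections to a stronger reading do stand. A reader might infer that the trial is underpowered on its own assumptions, or that it falls below a promised 80%. The document does not support this, for three reasons.

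- **No power is stated.** The 80% is back-solved, and so are two-sidedness and the baseline-adjusted model. The match to 158 per condition is good evidence for that combination but not proof. A one-sided change-score test at 85% power comes close to 317, and on that reading power at 144 per condition stays above 80%. Section 2.6.2 plans a difference-in-difference analysis, to which a change-score calculation is closer than a baseline-adjusted one.
- **The timing of the 30% is not given.** Section 2.3 has follow-up surveys at 1 and 3 months, and section 2.6.1 does not tie the 30% to either. If it is cumulative to the later survey, a 1-month comparison would lose fewer participants.
- **The consequence is small.** About 3 points of power are at stake. The endpoint, the analysis method and the type I error are untouched, and 412 would be enough if attrition turned out at 23% or less.

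**Conclusion.** The attrition step is wrong as written. With 30% loss, 412 recruits leave about 288 (144 per condition), 29 short of the 317 that the protocol says it needs. The consistent target is 453, or 454 for equal groups. This rests only on the figures in section 2.6.1 and on reading attrition as a share of those enrolled, which is how the article defines it.

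The cost in power is about 3 points: 80% to about 77% under a two-sided baseline-adjusted model, with similar losses under the change-score variants. Those power levels are conditional on assumptions the protocol does not state. This is a numerical correction that should be made, but it is not one on which the trial's validity depends.

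**What to change.** Replace the attrition sentence in section 2.6.1 with wording such as: *412 recruited with 30% attrition gives about 288 evaluable (144 per condition); 317 evaluable requires attrition of no more than 23%.* Add the power at 288, together with the power target, the sidedness of the test and the model used for the calculation. The investigators can take these from their own power calculator run, so no outside figure is needed.

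This costs a sentence or two and no extra participants, and 412 can stay wherever else it appears. The price is admitting slightly less power than the 317 implies. If recruitment allows, the alternative is to raise the target to 454 (227 per condition), which is 42 more participants. In that case the abstract, section 1.3 and section 2.3 need the same change.

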#### 2.6.2. Analytic plan

Quantitative analyses of the resulting pre- and post-workshop data will examine whether levels of CSA-related awareness and intention to use protective behaviors are greater for parents who participated in a Smarter Parents workshop in comparison to those who did not. As we will have longitudinal quasi-experimental data, we will use a difference-in-difference (DID) approach to analysis [38]. DID is appropriate when (a) randomization at the individual level is not possible and (b) the goal is to examine the effect of a specific intervention by comparing changes overtime among those who received the intervention (experimental) and those who did not (control). Using the DID regression framework, meditation analyses will examine potential differential effects by parent characteristics (e.g., demographics, initial parenting strategies [KOPSS] and actual use of protective and preventive behaviors [PBQ]).

To understand the impact of recruitment materials on parental engagement, we will first qualitatively code the strategies used on recruitment materials provided by the sites (e.g., theoretical framing, image, testimonial, incentive, etc.). We will quantify which strategies were used most consistently across the experimental site. We will also map types of ads used by the sites to registration/attendance numbers reported on the implementation forms. Participant responses on the satisfaction form (e.g., “Do you have any suggestions on how to promote Smarter Parents in your community?”) will be coded thematically to inform sites recruitment efforts in the future. All data will be made available in the lead authors’ university data repository once the study is complete.

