## 2. Methods

### 2.1. Workshop implementation

Implementation of the workshop by the nine community-based organizations is supported by grants awarded by a Pennsylvania state-government agency. Selected via competitive application process the sites represent victims service agencies, child advocacy centers, and youth serving organizations. Facilitators (*n* = 2 per site) were trained to deliver the *Smarter Parents* workshop in August of 2023. Once certified, facilitators could train other facilitators at their site to deliver the workshop; certification for all facilitators was provided by the research team. Implementation began in earnest across all sites in early 2024.

As designed, the group-based *Smarter Parents* workshop may be delivered in-person (i.e., at the site, a library, or other community location) or online (via interactive videoconferencing software such as Zoom). To achieve model fidelity, it is required each workshop follow a 1:10 ratio wherein there is 1 facilitator for every 10 participants (max. 20 participants). Parent participants will receive a physical copy of the *Smarter Parents* Parent Handbook at in-person workshops, or an electronic copy (i.e., PDF sent via email) for online workshops. Facilitators will submit an implementation form for each scheduled workshop regardless of the number of registrants or participants. This form documents the date and time of the workshop, number of registrants, number of participants, aspects of fidelity, rating of participant engagement, and documentation of any unforeseen circumstances (e.g., disclosure, interruption, etc.). Facilitators are encouraged to attend monthly learning collaborative style implementation meetings held to highlight successes and address any challenges or concerns that have risen for facilitators during implementation processes. As this is an active implementation, sites are responsible for marketing and advertising. Per their grants, sites are able to provide meals, transportation, childcare, or incentives (e.g., gift cards, gas cards) for workshop participants. All marketing and promotional materials will be sent to the research team on a quarterly basis for examination in Aim 3 of the current study.

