### 2.3. Experimental procedures

All procedures were approved by the Institutional Review Boards at New York University and the Pennsylvania State University. A waiver of written consent was obtained wherein if participants decided to move forward in the survey after viewing the consent form, they were providing their implied consent. Study recruitment launched on May 1, 2024, and the targeted date for finalizing recruitment is December 31, 2024. As randomization at the site level is not feasible, parents who participate in the *Smarter Parents* workshop with one of our 9 partner sites will comprise the experimental group (target *n* = 206). Control participants (i.e., those who do not receive the *Smarter Parents* workshop; target *n* = 206) will be recruited from generalized recruitment ads distributed by community partners in Pennsylvania (not engaged in Project Safe and Smart) at similar agencies to those providing the workshop and recruiting the experimental group.

Participants, whether experimental or control, will complete three 15-minute surveys administered on REDCap (Research Electronic Data Capture) [29]: (a) Survey 0 (i.e., baseline), upon registration for the research; (b) Survey 1, completed 1-month after Survey 0 and workshop attendance, where applicable; and (c) Survey 2, 3-month follow-up (Fig 1). Participants will scan a QR code located on the recruitment materials to bring them to the screening form which then automatically proceeds to the consent form and will be provided a copy for download. Advancing to the first survey indicates their implied consent. Each subsequent survey will be sent at the appropriate timepoint via unique REDCap link to the email address the participant provides in Survey 0. Email reminders to complete each survey will be sent every two days up to a total of five times per participant.

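### The sample size assumes independent participants although the workshop is delivered in groups at nine sites; unless clustering of change is modelled, the DID standard error will be too small whenever the ICC is positive

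*Protocol article*

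**What the plan says.** **Delivery.** Section 2.1 of the protocol article describes a group workshop run by nine community organizations, each with its own trained facilitators, in person or by videoconference. On group size, "there is 1 facilitator for every 10 participants (max. 20 participants".

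**Allocation.** Section 2.3 begins its account of the groups with "As randomization at the site level is not feasible". The experimental group is whoever attends at one of the nine partner sites. Controls are recruited through similar agencies that are not part of the project. Each agency therefore supplies one arm only.

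**Sample size.** Section 2.6.1 takes a standardized effect of .2 and a significance level of .10. For the repeated measurements, the authors "assumed a conservative pre-post correlation of .7". The calculation "indicated a need for 317 total participants (158 per condition"), raised to 412 for 30% attrition. No ICC, design effect or number of clusters appears among the inputs, and neither the power nor the sidedness of the test is stated.

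**Analysis.** Section 2.6.2: "As we will have longitudinal quasi-experimental data, we will use a difference-in-difference (DID) approach to analysis". It compares changes over time between the groups in a regression framework. It does not list the terms of the model or say how standard errors are obtained.

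**The concern.** Parents in the same workshop share facilitators, discussion, role-play and format. Parents at the same site also share a community and whatever happens locally between surveys. Differencing removes stable differences between agencies, but not shared influences on change, and change is what the DID compares. Because exposure is fixed at the level of the agency, any such correlation enters the variance of the treatment contrast in full.

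Two things are at stake. The planned number carries less information than the calculation credits it with, so power is overstated. And if the analysis ignores the correlation, the reported standard error is too small and the false-positive rate exceeds a significance level that is already liberal at .10.

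**Working it through.** **Inputs from the protocol article.** d = .2, r = .7, α = .10, 158 per condition (section 2.6.1); nine experimental sites (section 2.3); at most 20 parents per workshop (section 2.1).

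**Assumptions.** Two-sided test and 80% power, both inferred because they reproduce the stated figure. The ICC, for the baseline-adjusted outcome within site, is taken as .01 to .05.

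**Step 1: reproduce the stated figure.** For independent participants with baseline adjustment, the residual variance is 1 − r² = 1 − .49 = .51. Then

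n per arm = 2 × (1.645 + 0.842)² × .51 / .2² = 157.7, rounded up to 158.

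With the t distribution in place of the normal, the result is 158.3 per arm, or 316.7 in total, which rounds up to 317. Both stated figures are recovered with a design effect of exactly 1.

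**Step 2: design effect per site.** Average cluster size m = 158 / 9 = 17.6, and DE = 1 + (m − 1) × ICC.

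**Step 3: effect on the contrast, clustering in the experimental arm only.** The variance of the difference is multiplied by VF = (DE + 1) / 2. The true standard error is √VF times the unadjusted one, which is √(2 × .51 / 158) = .0803.

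- True type I error of the unadjusted test = 2 × [1 − Φ(1.645 / √VF)]
- Power of a test using the correct standard error ≈ Φ(.2 / (.0803 × √VF) − 1.645)

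| ICC (assumed) | DE | VF | √VF | Type I error, unadjusted | Power at 158 per arm | n per arm for 80% |
|---|---|---|---|---|---|---|
| 0 | 1.00 | 1.00 | 1.00 | .100 | 80% | 158 |
| .01 | 1.17 | 1.08 | 1.04 | .114 | 77% | 171 |
| .02 | 1.33 | 1.17 | 1.08 | .128 | 75% | 184 |
| .05 | 1.83 | 1.41 | 1.19 | .167 | 67% | 223 |

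**Step 4: sensitivity to the level and extent of clustering.**

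- *Workshop level only, few completers.* With 5 study completers per workshop (an assumption, since only the maximum attendance is given), DE is 1.04 to 1.20 for ICC .01 to .05. Type I error is .103 to .117 and power 79% to 77%.
- *Both arms clustered alike.* VF = DE. For ICC .01 to .05, type I error is .128 to .224 and power 75% to 58%. This is speculative, because the number of control agencies is not given.

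**Step 5: few clusters.** The figures above use the normal critical value 1.645. With nine experimental clusters, a site-level critical value on 8 degrees of freedom would be 1.860, so a valid test would have somewhat less power than shown.

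**The case against.** The strongest reply is that section 2.6.2 is a short account in a journal article. It names DID and stops there. DID is compatible with mixed models and with clustered standard errors, and a full analysis plan that is not shown may specify either. This stands. A reader might infer that the plan commits to treating participants as independent in the analysis, and that its intervals will be too narrow. The documents do not support that: the section lists no model terms and no standard-error method. The inflation of type I error is therefore conditional. The sample-size half is not affected, because section 2.6.1 gives its inputs and the figure they produce, and that figure allows nothing for clustering.

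It can also be said that the ICC is unknown, that only the ICC of change matters once stable differences are removed, and that after one two-hour session it could be close to zero. This stands too, and is why a range starting at .01 is shown. Clustering at workshop level with few completers each would also shrink the effect, as Step 4 shows.

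A reader might take the both-arms figures as the likely case. They have the least support: controls attend no group session, answer general advertisements and complete the surveys individually.

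Finally, the protocol's power is open to question on two other grounds: how attrition was applied, and the use of a baseline-adjusted variance where a DID change score is planned. Neither is clustering, so the working stays on the protocol's own 158 per arm to keep those losses out of the figures.

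**Conclusion.** The point holds in a conditional form. The documents establish that delivery is in groups, that arm is nested in agency, and that 317 (158 per condition) is the answer for independent participants. They do not establish how the DID standard error will be computed.

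If the ICC of change is positive, power is lower than planned. With 17.6 participants per site, an ICC of .01 to .05 and clustering in the experimental arm only, it is about 77% to 67% instead of 80%. If, in addition, clustering is not modelled, the unadjusted standard error is too small by a factor of 1.04 to 1.19 and the nominal .10 test has a type I error of about .11 to .17.

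These sizes rest on the assumed ICC, equal numbers per site, the inferred two-sided 80% basis, and normal critical values. The shortfall is worth correcting, but it is moderate over this range and could be small.

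**What to change.** 1. **Link every participant to a cluster.** Record workshop and recruiting agency for each person. For the experimental group, sites already verify attendance and file a form for each workshop, so part of this may exist. Controls already enter by QR code, so an agency-specific link would be enough. This is best done while recruitment is open, since a control's agency may be hard to recover later.
2. **State the model.** Fit the DID as a partially nested mixed model (participants within workshops within sites in the experimental arm), or use agency-clustered standard errors with a small-sample correction suited to nine experimental clusters, such as a wild cluster bootstrap.
3. **Restate power.** Keep N as it is and report power over a range of ICCs, with the assumed cluster sizes.

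The cost is one tracking field and a change of model. Intervals will be wider where the ICC is positive, and the stated power will look less favourable.
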